### Participant timeline {13}

The inclusion will last 24 months. The patient participation, from the surgery day to the end of follow-up, will be 24 months (Table 3).

**Table 3 Tab3:** Participant timeline

	**Pre-inclusion visit (V0)** **D0 -9 to 120 days**	**Inclusion visit (V1)** **D0 -2 to 90 days**	**Surgery (V2)** **D0**	**3 months follow-up (V3)** **D0 + 90 days ± 30**	**12 months follow-up (V4)** **D0 + 360 days ± 30**	**24 months follow-up (V5)** **D0 + 720 days ± 30**
ENROLMENT:						
Patient information	X					
Eligibility screening		X				
Urinary pregnancy test		X				
Informed consent		X				
Allocation		X				
INTERVENTION:						
Radiation exposure measurement			X			
ASSESSMENT:						
CT scan			X^a^		X	X
Full-spine x-ray or EOS		X		X	X	X
ODI score		X		X	X	X
Pain on VAS		X		X	X	X
HAD scale		X		X	X	X
Sensory status		X		X	X	X
Motor status (MRC)		X		X	X	X
EQ5D-5L questionnaire		X		X	X	
Complications			X	X	X	X
Concomitant treatment		X	X	X	X	X
Adverse events			X	X	X	X

^a^Postoperative day 1

### Sample size {14}

Patients are considered as “clusters” of screws, due to the inter-dependence on the placement of screws in the context of complex cases (e.g. morbid obesity, bone fragility). The required sample size of screws is calculated to compare the proportions of grade A placed screws (Gertzbein-Robbins classification) by robot-assisted versus conventional surgery in thoracolumbar arthrodesis. According to the literature, the proportion of grade A placed screws of conventional surgery is approximately 88% [3, 8], and we hypothesize that robot-assisted surgery will improve this proportion by 7%. Therefore, 725 screws per group are needed to detect a statistically significant difference in the proportion of grade A placed screws, assuming an intracluster correlation coefficient (ICC) of 0.3, with a power of 90% and a bilateral *α* of 5%. Based on the assumption that each patient is implanted with an average of 5 screws [4, 9, 10] and that 5% of patients will be randomized but not operated, the total number of patients to be randomized is 300 (150 patients per group). The sample size was determined using the Power Analysis & Sample Size (PASS) software 2021 (NCSS).

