## Introduction

### Background and rationale {6a}

There are many indications for thoracolumbar spinal arthrodesis, including deformities (scoliosis, kyphosis), spondylolisthesis, discopathy and spinal instability. Posterior arthrodesis with pedicle screw and rod placement has established itself as the reference technique since the 1980s. The accuracy of this surgical technique was improved by 2D fluoroscopy and then by 3D computer-assisted navigation (CAN), which made it possible to reduce extra-pedicular placement of screws and subsequent complications [1]. Furthermore, in the 2000s, spinal surgical robots were introduced, and these have evolved over the last decades to allow pre- and intraoperative planning (implant selection, optimal trajectory), robotic guidance and real-time 3D navigation [2] thanks to integrating CAN systems within the robotic platform.

Compared to freehand surgery, robotic surgery may result in better pedicle screw placement accuracy [3–5], reduction in intraoperative irradiation [4] and reduction in the length of stay (LOS) [4]. A meta-analysis by Staartjes et al. [6] revealed significantly fewer revisions for screw malposition following thoracolumbar arthrodesis using robotic or CAN guidance compared to freehand surgery, which may imply an association between pedicle screw placement accuracy and revision rates. However, there are few randomized controlled trials (RCT) that have assessed pedicle screw placement accuracy of the newest generation of spinal robots with integrated CAN.

Pedicle screw placement accuracy is an objective outcome measure that can be assessed immediately following surgery and, unlike patient-reported outcomes, does not depend on patient expectations, co-morbidities or follow-up rates. Pedicle screw placement is also one of the most frequently reported outcomes of spinal arthrodesis and facilitates comparisons of surgical methods across the literature.

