### Data collection and management

#### Plans for assessment and collection of outcomes {18a}

The following datasets will be defined:Intention-to-treat (ITT; effect of assigning the treatment): This dataset will include all enrolled patients who undergo surgery, who will be analysed in their assigned groups, irrespectively of possible protocol deviations or crossovers between treatment arms.Per-protocol (PP; effect of receiving the treatment): This dataset will include enrolled patients who undergo their assigned treatment without major deviations from the protocol (deviations that could impact the assessment of the primary endpoint).

The following information will be included on the e-CRF after enrolment and allocation:Patients’ characteristics: age (years), sex, weight (kg), height (cm) and pregnancy testRadiological data: screw placement accuracy, screw fracture/loosening and superior-level facet joint violation on CT images on postoperative day 1 and at 12- and 24-months follow-upClinical data: intervention time, LOS, EBL, surgeon’s intraoperative radiation exposure, sensory and motor function at inclusion and all follow-up visitsFunctional outcomes: pain, ODI, HAD, EQ5D-5L at inclusion and all follow-up visitsMedical costs at 12 months follow-up

The primary outcome will be assessed for both datasets (ITT and PP). The secondary outcomes will be assessed on the ITT dataset.

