## Statistical methods

### Statistical methods for primary and secondary outcomes {20a}

The quantitative variables will be described by the number of values entered, the number of missing data, the mean, the standard deviation, the median, the 1st and 3rd quartiles, the minimum and the maximum. The qualitative variables will be described by the number of values entered, the number of missing data, the frequency, the percentage of each modality and the 95% confidence interval (CI) of each modality, if relevant. The type I error (*α*) is set at 5% with a two-tailed analysis for the entire study. No management of multiplicity will be carried out. The secondary outcomes will be analysed on an exploratory basis. The primary outcome (proportion of grade A placed screws according to Gertzbein-Robbins classification on postoperative day 1) will be described by group (robot-assisted vs. conventional surgery) and compared using a marginal logistic model (taking into account screw clusters in the same patient) including the group and the randomization stratification factor (long-segment fusion vs. short-segment fusion). The results of the marginal logistic model will be interpreted in terms of adjusted odds ratio (aOR) accompanied by the 95% CI. Intervention time, OR occupancy time, LOS, EBL and surgeon’s intraoperative radiation exposure will be described by group (robot-assisted vs. conventional surgery) and compared using an analysis of variance (ANOVA) including the group and the randomization stratification factor (long-segment fusion vs. short-segment fusion). Radiological stability (signs of screw fracture/loosening), superior-level facet joint violation, complication and reoperation rates will be compared using logistic regression including the group and the stratification factor of the randomization (long-segment fusion vs. short-segment fusion). Functional outcomes (ODI, pain, HAD) will be compared using an analysis of covariance (ANCOVA) including the group, the score at inclusion and the randomization stratification factor (long-segment fusion vs. short-segment fusion); this analysis will be carried out at each evaluation time (3-, 12- and 24-month follow-up). The evaluation of sensory status and motor status will be compared using a Cochran-Mantel-Haenszel test including the group and the stratification factor of the randomization (long-segment fusion vs. short-segment fusion); this analysis will be carried out at each evaluation time (3-, 12- and 24-month follow-up). The cost-utility analysis will be carried out according to the recommendations of the French National Authority for Health (HAS) [11], based on QALYs (lifespan weighted by health-related quality of life), derived from the EQ5D-5L. All direct medical costs will be measured over 12 months following hospital discharge. The incremental cost-utility ratio (difference in costs divided by the difference in QALYs) between robot-assisted surgery and conventional surgery will be determined at 12 months along with their 95% CIs. All statistical analysis will be performed using the latest version of the SAS software.

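### Optional precision gain: the primary model is valid and adequately powered, but leaves out baseline BMI and age, which the trial can take from data it already records

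*Protocol article*

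**What the plan says.** In the protocol article, Sample size {14} explains that screws within a patient are not independent, "due to the inter-dependence on the placement of screws in the context of complex cases (e.g. morbid obesity, bone fragility"), and sizes the trial "assuming an intracluster correlation coefficient (ICC) of 0.3".

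Statistical methods {20a} fixes the primary analysis as a "marginal logistic model (taking into account screw clusters in the same patient) including the group and the randomization stratification factor", the factor being long- versus short-segment fusion. No other baseline term is listed.

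Plans for assessment and collection of outcomes {18a} places "age (years), sex, weight (kg), height (cm") on the e-CRF, so BMI can be derived for every patient. No measure of bone fragility appears in that list. Eligibility criteria {10} exclude a BMI of 40 kg/m² or more. Sequence generation {16a} stratifies on the planned number of screws only.

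**The concern.** An intracluster correlation of 0.3 with five screws per patient more than doubles the screws required, so the plan treats between-patient variation as large. A marginal model gives correct standard errors in the presence of that variation but does not reduce it. If some of it relates to body size, as the sample-size section suggests by naming obesity, a baseline term for BMI would recover part of the lost information from data already collected. BMI and age are also not balanced by design, so a chance difference between the arms would move the observed primary estimate.

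What is at stake is precision in the one confirmatory test. Neither bias nor the type I error is in question.

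**Working it through.** **Inputs**, all from Sample size {14}: "the proportion of grade A placed screws of conventional surgery is approximately 88"%, "we hypothesize that robot-assisted surgery will improve this proportion by 7"% (so 0.88 against 0.95), "with a power of 90% and a bilateral *α* of 5"%, ICC 0.3, five screws per patient on average, 5% randomized but not operated, 150 patients per group.

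**1. The plan's own figure.**
- Design effect: 1 + (5 − 1) × 0.3 = 2.2.
- Independent screws per group, unpooled variance: (1.960 + 1.282)² × (0.88 × 0.12 + 0.95 × 0.05) / 0.07² = 328.3.
- Clustered: 328.3 × 2.2 = 722.3 screws, or 144.5 patients. Rounded up, 145 patients × 5 = 725 screws, as stated.
- Non-operated patients: 145 / 0.95 gives 153 per group, 306 in total. The stated 300 is 2% below that.

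**2. Power without covariates.** In closed form, power is 0.898 at 725 screws per group, and 0.893 at 150 × 0.95 = 142.5 operated patients per group. The plan therefore reaches its target, within rounding, without any gain from adjustment.

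**3. What adjustment could add.** Trials were simulated with 143 patients per arm, five screws each, 88% against 95%, and a normal patient effect giving a binary ICC of 0.30 at 88% (0.24 at 95%). The analysis was a logistic fit with cluster-robust variance. One standard normal covariate stood in for BMI and age and explained an assumed share of the latent between-patient variance. Entries are power without → with the covariate.

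| Share explained | 3,000 trials | 3,000 trials, repeat | 6,000 trials, repeat |
|---|---|---|---|
| 0% | 92.5 → 92.5 | 92.1 → 92.2 | 91.9 → 91.9 |
| 10% | 91.2 → 92.3 | 91.6 → 92.8 | 91.8 → 92.2 |
| 20% | 91.4 → 94.3 | 92.1 → 93.6 | 91.4 → 93.6 |
| 30% | 92.3 → 95.4 | 91.8 → 94.8 | 91.5 → 95.2 |

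Unadjusted power cannot depend on the share explained, so its spread of 91.2 to 92.5 shows the Monte Carlo noise (about 0.5 points per entry at 3,000 trials).

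With a stronger patient effect (ICC averaging 0.3 over the two rates), 6,000 trials per setting gave 90.0 → 90.0, 90.3 → 91.4, 89.7 → 91.8 and 90.2 → 93.8 for the same four shares. A GEE run of 600 trials on 285 patients gave 89.8 → 91.2 at 10% and 88.5 → 94.2 at 30%. Its Monte Carlo error is about 1 point, and the larger runs do not support so big a gain at 30%.

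Type I error at 20% explained was 5.0 to 5.3% in the larger runs, with and without the covariate. In the GEE run it was 4.2 to 4.5% unadjusted and 4.5 to 5.7% adjusted.

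**4. Chance imbalance.**
- One standard error of the difference in a standardized covariate is √(2/143) = 0.118.
- At 20% explained, the latent shift is √(0.554 × 0.20) × 0.118 = 0.039, where 0.554 is the latent patient variance in these simulations.
- Multiplied by the normal density at the two thresholds (0.200 at 88%, 0.103 at 95%), this is 0.8 and 0.4 percentage points, against 7 hypothesized.
- The planned standard error of the difference is √(0.1531 × 2.2 / 712.5) = 0.022, or 2.2 points. Such a shift is well inside the uncertainty already reported.

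**5. Room for extra terms.** Expected screws not graded A: 725 × 0.12 = 87 plus 725 × 0.05 = 36, or 123 in all. That is enough for two more coefficients.

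The simulations hold five screws fixed, omit the fusion stratum and use an uncut normal covariate.

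**The case against.** The case for leaving the model alone is strong, and most of it stands. The sample-size sentence names obesity and bone fragility to justify clustering, and the plan answers it twice: through the ICC and through the marginal model. Randomization removes bias from omitted covariates, and the confidence interval already covers chance imbalance. Adjusting for the stratification factor alone is a standard choice. The link to recorded data is thin: bone fragility is not on the list, the BMI exclusion removes the morbid end of obesity, and age and sex are nowhere called prognostic. A supplementary adjusted analysis may sit in a SAP that is not shown. Nor is adjustment wholly free, since odds ratios are non-collapsible and the reported effect would change meaning.

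What survives is narrow. The primary model's terms are fixed in the article, BMI is available for everyone, and the plan itself cites obesity. In the simulations, adjusting for a covariate that explained nothing cost no power.

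A reader might go further and set the Background statement that accuracy "does not depend on patient expectations, co-morbidities or follow-up rates" against the sample-size section, inferring a contradiction that led the authors to leave covariates out. The documents do not support this. That statement contrasts an objective CT measure with patient-reported outcomes. Its mention of co-morbidities is loose, but nothing connects it to the choice of model.

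**Conclusion.** This is an optional improvement, not a defect. The primary model is valid and meets its planned power to within about a point. Prespecified adjustment for baseline BMI, with age as a proxy, would add about 0 to 1 point of power if the two explain 10% or less of the between-patient variance, and about 2 to 3.5 points at 20 to 30%. It would also remove most of an imbalance effect of roughly 0.4 to 0.8 percentage points per standard error of imbalance at 20% explained.

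All of this rests on the assumed share, for which the documents give no figure. The BMI cut-off and the lack of a bone-fragility measure argue for the lower part of the range. It would be wrong to infer that the unadjusted analysis is biased or that the trial is underpowered for want of covariates. The case is firmest for BMI and weaker for age; nothing in the documents makes a case for sex.

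**What to change.** Before any comparative data are seen, state that the primary marginal logistic model contains group, fusion stratum, baseline BMI (continuous) and age (continuous). Keep the group-plus-stratum model as a named sensitivity analysis. Report a standardized risk difference beside the adjusted odds ratio, so that the result can be read against the hypothesized 7 points.

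The change takes one sentence in the analysis section and no new data. The costs are an odds ratio conditional on BMI and age, and possibly a formal amendment: the article gives a recruitment start of 26/12/2022, and its section on protocol amendments {25} requires a favourable ethics opinion for substantial modifications. Because surgeons and patients know the allocation, the change should be dated and shown to precede any comparison of the arms. If that is no longer possible, keep the present primary model and label the adjusted model as the sensitivity analysis.

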### Assignment of interventions: allocation

#### Sequence generation {16a}

Before randomization, patients will be stratified according to the planned number of screws needed for surgery, with short-segment fusion comprising four to six screws (two to three vertebrae) and long-segment fusion comprising at least eight screws (more than three vertebrae). The randomization sequence will be generated before the commencement of the study separately for each stratum with the R software and will be integrated into the data management software (REDCap).

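### By the plan's own inputs, 300 patients give about 712 screws per group, not the 725 required, and the 725 assumes exactly five screws in every patient; the power cost is small.

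*Protocol article*

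**What the plan says.** The protocol article, Sample size {14}, treats each patient as a cluster of screws. Its inputs are as follows.

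- Control rate: "the proportion of grade A placed screws of conventional surgery is approximately 88" per cent.
- Effect: "we hypothesize that robot-assisted surgery will improve this proportion by 7" per cent.
- Clustering: "assuming an intracluster correlation coefficient (ICC) of 0.3".
- Error rates: "with a power of 90" per cent and a two-sided 5% level. Statistical methods {20a} confirms that the level "is set at 5% with a two-tailed analysis for the entire study".

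From these it states that "725 screws per group are needed to detect a statistically significant difference in the proportion of grade A placed screws". It then takes a mean of 5 screws per patient and 5% of patients who are randomized but never operated, and arrives at: "the total number of patients to be randomized is 300 (150 patients per group").

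Two other sections bear on this. Sequence generation {16a} stratifies on the planned number of screws: short fusions have 4 to 6, against "long-segment fusion comprising at least eight screws (more than three vertebrae"). Section {18a} restricts the intention-to-treat set to patients who undergo surgery, so non-operated patients contribute no screws.

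**The concern.** The stated number of patients does not follow from the stated number of screws once the plan's own 5% loss is applied. In addition, the screw requirement is reproduced only with a constant cluster size, which the stratification rules out as soon as patients enter both strata. Clusters of unequal size carry less information than equal ones with the same mean.

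A null or borderline result will be read against the published 725 screws and 90% power. Those figures should therefore match what the design is expected to deliver. The matter affects the description of power, not the validity of the eventual estimate or its confidence interval.

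**Working it through.** **Inputs.** From Sample size {14}: p1 = 0.88, p2 = 0.95 (the 7% read as percentage points, which reproduces the plan's figure), ICC = 0.3, mean cluster size m = 5, loss 5%, power 90%, two-sided α = 0.05. Allocation is 1:1 (Trial design {8}).

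**Step 1: reproduce 725.**
- Unpooled two-proportion formula: n = (1.960 + 1.2816)² × (0.88 × 0.12 + 0.95 × 0.05) / 0.07² = 10.507 × 0.1531 / 0.0049 = 328.3 independent screws per group.
- Design effect with constant size 5: 1 + (5 − 1) × 0.3 = 2.2.
- 328.3 × 2.2 = 722.3 screws; 722.3 / 5 = 144.5, rounded up to 145 patients, and 145 × 5 = 725. The match is exact. The formula with pooled variance under the null gives about 729.

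**Step 2: apply the 5% loss.**
- Forward: 145 / 0.95 = 152.6, so 153 per group, 306 in total.
- Backward: 150 × 0.95 = 142.5 operated patients; 142.5 × 5 = 712.5 screws, 12.5 (1.7%) below 725.

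**Step 3: power with equal clusters.** Power = Φ(0.07 / √(0.1531 / n_eff) − 1.96), with n_eff = screws / 2.2.
- 725 screws: n_eff = 329.5, power 90.1% (pooled 89.8%).
- 712.5 screws: n_eff = 323.9, power 89.6% (pooled 89.3%).

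The loss costs about 0.5 percentage point.

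**Step 4: unequal clusters at mean 5.** The article gives neither a coefficient of variation (CV) nor the share of long fusions, so the mixes below are assumptions. With every screw weighted equally, the design effect is 1 + ((1 + CV²) × m − 1) × 0.3. With exchangeable weighting, n_eff is the sum over patients of size / (1 + (size − 1) × 0.3). Both use 142.5 patients per group and the unpooled formula; pooled values are about 0.3 point lower.

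| Screws per patient (share) | CV | Design effect | Power, equal screw weights | Power, exchangeable |
|---|---|---|---|---|
| 5 (100%) | 0 | 2.20 | 89.6% | 89.6% |
| 4/6 (50/50%) | 0.20 | 2.26 | 88.8% | 89.3% |
| 4/6/8 (60/30/10%) | 0.27 | 2.31 | 88.2% | 89.2% |
| 4/8 (75/25%) | 0.35 | 2.38 | 87.2% | 89.0% |

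With a minimum of 4 screws and a mean of 5, at most 25% of patients can have 8 or more (4 × 0.75 + 8 × 0.25 = 5). The last row is therefore a boundary case.

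**Step 5: mean above 5.** The same 142.5 patients then carry more screws.

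| Screws per patient (share) | Mean | Power, equal screw weights | Power, exchangeable |
|---|---|---|---|
| 4/6/8 (50/35/15%) | 5.3 | 88.6% | 89.7% |
| 4/6/8/10 (50/30/10/10%) | 5.6 | 88.2% | 90.0% |
| 4/6/8/12 (55/25/10/10%) | 5.7 | 87.0% | 89.9% |
| 4/6/8/10 (40/35/15/10%) | 5.9 | 88.9% | 90.4% |

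**The case against.** The strongest reply is that this is rounding. Six patients in 306 is 2%, and 89.6% rounds to 90%. The inputs are themselves round planning values: with 712.5 screws, an ICC of 0.29 instead of 0.30 already gives 90.1%. That is right as to size, and it is why the point is minor. It does not make 300 follow from 725, 5 and 5%.

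A reader might go further and infer that the trial fails its 90% target or is seriously underpowered. The documents do not support that. On the plan's own inputs power is about 89.5%, and any larger loss depends on a size distribution that the article does not give. Figures near 85% need an assumed long tail together with equal weighting of screws. For example, 4/10 screws in 83/17% of patients has mean 5 and gives 85.5% on that weighting, but 88.7% with exchangeable weighting. Holding the mean at 5 also fixes the direction of the result, since more long fusions would raise the screw count and recover part of the loss. Even so, a heavy tail can outweigh the gain: 4/6/12 in 55/30/15% (mean 5.8) gives 86.4% with equal screw weights and 89.9% exchangeable.

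A reader might also take the unnamed working correlation of the marginal logistic model in {20a} as an error. It is commonly fixed in the statistical analysis plan, which is not shown, so it is not a fault of the protocol.

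**Conclusion.** The point holds as a small inconsistency, not as a failed power calculation. The inflation result (306 instead of 300, or 712.5 screws instead of 725) needs no outside assumption and costs about half a point of power.

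The constant cluster of 5 is at odds with the strata, and at a fixed mean of 5 any variation in size lowers power. How far is an assumption: roughly 87–89% under the illustrative mixes at mean 5 (about 89% with exchangeable weighting), and about 87–90% for most mixes with a higher mean. All of these figures take the plan's ICC, rates and 5% loss as given.

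**What to change.** Keep 300 patients and restate Sample size {14}:

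- about 712 expected screws per group after the 5% loss;
- about 89.5% power with equal clusters;
- slightly lower power, in the high 80s, when the number of screws varies, with the assumed distribution of screws per patient written down.

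Optionally, the statistical analysis plan could specify an exchangeable working correlation for the primary model, which recovers most of the loss from unequal sizes in these mixes. This is a suggestion, not a correction to the protocol.

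The cost is a few restated figures and one sentence on the distribution. No patients are added, and neither the design nor the conduct of the trial changes.
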